### Model estimation

Model coefficients will be estimated using Weibull accelerated failure time models to calculate 5-year risk of type 2 DM. This parametric model was chosen since it allows for the calculation of more clinically meaningful parameters, including predicted survival time for different follow-up periods.

A full model, including all predictors and important interactions, will be developed in the first instance. Since the practical application of the full model may be time-consuming for intended users, we will derive a less complicated model by applying Ambler’s step-down approach [45]. This approach involves the regression of the derived prognostic index from the full model in the predictors. Predictors are subsequently dropped that produce the smallest reduction in *R*^2^. This procedure will be repeated until the exclusion of any further predictors would lead to a *R*^2^ value below 0.95. This approach will ensure that variables that contribute very limited information to the model are removed. We will verify our model building approach in exploratory analyses by applying least absolute shrinkage and selection operator (LASSO) to conduct variable selection and regularization.

### Assessment of RPM discrimination

Discrimination, which describes the models ability to distinguish between women who did and did not develop type 2 DM, will be assessed using C-statistics. C-statistics will be calculated at various time points (e.g., 1 year, 2 years, 5 years). The clinical usefulness of the RPM will be quantified using the net benefit approach [46].

### Assessment of RPM calibration

Overall model calibration describes the agreement between observed and predicted risks. Calibration will be assessed using calibration plots and estimation of calibration slopes and calibration-in-the-large values in each imputed dataset. Calibration curves will be generated in each imputed dataset and combined into a single plot. Calibration slopes will be estimated at fixed time-points by regressing the observed risk of type 2 DM on the predicted prognostic index. Calibration-in-the-large will be estimated by comparing the mean observed risk estimated using the Kaplan-Meier method with the mean predicted risk. Calibration will be assessed within predefined groups, including by GDM status, ethnicity and age. Formal statistical testing of calibration using Hosmer-Lemeshow goodness of fit tests will not be performed, due to the large sample size.

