### Participants

The derivation cohort will consist of all women aged between 16 and 50 years (at index pregnancy) whose pregnancy resulted in a live birth or still birth in Ontario between 1st April 2006 and 31st March 2014. No minimum duration of pregnancy was required for inclusion into the derivation cohort. For women who had multiple pregnancies during this period, the first pregnancy occurring during the accrual window will be selected. The influence of this choice of pregnancy will be examined in sensitivity analyses involving the development and validation of models in separate cohorts containing a randomized choice of pregnancy. Women with pre-pregnancy DM as ascertained using the ODD and available variables in BORN indicating pre-existing DM will be excluded from the derivation cohort. Women who were ineligible for the Ontario Health Insurance Plan or were a non-Ontario resident in the 2 years prior to index date will be excluded since predictor and outcome data for these women will be incomplete. Index date is defined as 6 months post-partum. Women who had a second pregnancy prior to the index date and women who died prior to index will also be excluded.

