### Main predictors

Table 1 lists the predictors and the pre-specified functional forms for each.

**Table 1 Tab1:** Pre-specification of predictors for risk prediction model

Variable type	Variable	Specification	df
Demographics	Age at index	Continuous variable	1
	Income quintile	Five categories	4
	Rurality	Binary: yes/no	1
	Immigrant status	Three categories (non-immigrant, previous (over 10 years ago), recent (10 years or less)	2
	Ethnicity	Three categories (South Asian, Chinese, Other)	2
Lifestyle	Pre-pregnancy BMI, kg/m^2^ (self-reported)	Continuous	1-3
Lifetime Health history	Previous mental health condition	Binary: yes/no	1
	Previous cardiovascular disease	Binary: yes/no	
Prior pregnancy history	Parity	Five categories (0, 1, 2, 3, > 3)	4
	Gravidity	Four categories (1, 2, 3, > 3)	3
	Previous GDM	Three categories: yes/no/NA	2
	Previous gestational hypertension or preeclampsia	Three categories: yes/no/NA	2
Index pregnancy	50 g oral glucose challenge test, mmol/L	Continuous	1-3
	GDM	Binary: yes/no	1
	Preeclampsia	Binary: yes/no	1
	Gestational hypertension	Binary: yes/no	1
	Caesarean-section	Three categories: planned/emergency/no	1
	Premature delivery	Binary: yes/no	1
Newborn	Birthweight	Continuous (for women with a multi-fetal birth, the child with the higher birthweight will be used)	1
	Large for gestational age (LGA) birthweight > 90th	Binary: yes/no (for women with a multi-fetal birth, any child with a record for LGA will be used)	1

Choice of the candidate predictors was informed by a systematic literature review, consultation with the project advisory board, clinicians, and the availability of the predictors within the study’s data sources. To enhance usability, predictors of the model were also chosen based on their likely availability to intended users of the model. Continuous variables with limited variation and binary variables with small counts will be excluded. While categorical variables have been pre-specified, frequency distributions will be examined and categories may be combined where there are small numbers. Interactions between all predictors and each of age, GDM and ethnicity will be considered for inclusion into the model due to expected differences in the effect of these predictors by the selected variables. Interactions which improve model fit will be included in the final model.

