### Outcome

Women will be followed-up for the incidence of type 2 diabetes. The incident onset of type 2 DM will be ascertained using a validated definition [34]. That algorithm requires one hospital record including a diabetes-specific International Classification of Disease code (ICD) OR two physician claim records relating to diabetes treatment within 1 year of each other, OR a dispensing record for an anti-diabetic drug from the Ontario Drug Benefit. According to this definition, diabetes records occurring between 120 days before or 180 after a hospital or primary care record of pregnancy care are considered to relate to gestational diabetes and are excluded.

Where physician claim records are used to ascertain DM status, DM diagnosis date is set to the date of the first visit. The validated definition has a sensitivity of 90.0%, a specificity of 97.7%, and a positive predictive value of 82.6%. Women will be followed up from index date until the earliest of incident diabetes, death, new pregnancy conception date, or study end-date (31st March 2019).

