### External validation

We will externally validate the algorithm using data from a population-based pregnancy cohort from Alberta, the Alberta Vital Statistics–Birth database [47]. This database is populated by maternal, pregnancy, and neonatal data and is linked to hospital admissions records (Discharge Abstract Database), emergency room/outpatient clinic visits records (the Ambulatory Care Classification System (ACCS)), and physician office visit records (Fee-for-Service Claims (CLAIM)). Linkage to the Alberta Health Care Insurance Population registry provides demographic data including ethnicity and rurality. Diabetes will be ascertained using ICD-9 and ICD-10 codes in hospitalization, ACCS, or CLAIM records. The RPM will be applied in this cohort to estimate 5-year risk of RPM in this external population. The predictive performance of the RPM will be assessed by estimating the previously described measures of calibration and discrimination. Where appropriate, the RPM model will be re-calibrated by adjusting the baseline hazard and the mean values of the predictors to that of the external validation cohort [48].

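### Overall calibration-in-the-large sets an unweighted Kaplan-Meier risk against the mean predicted risk, which is biased if censoring at a new conception depends on the model's predictors

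*Protocol article*

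**What the plan says.** Under Assessment of RPM calibration, the protocol article defines the overall measure: "Calibration-in-the-large will be estimated by comparing the mean observed risk estimated using the Kaplan-Meier method with the mean predicted risk". It mentions no weighting, stratification or covariate adjustment for this measure. The same section also plans calibration plots, calibration slopes, and calibration within groups defined by GDM status, ethnicity and age. It rules out Hosmer-Lemeshow testing.

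Under Outcome, follow-up is defined: "Women will be followed up from index date until the earliest of incident diabetes, death, new pregnancy conception date, or study end-date". Under Participants, women are aged 16 to 50, and for those with several pregnancies "the first pregnancy occurring during the accrual window will be selected", so a later conception ends follow-up. Also, "Index date is defined as 6 months post-partum". Table 1 lists age, parity and GDM as predictors. Model estimation fixes a Weibull accelerated failure time model for 5-year risk.

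Under External validation, the calibration measures already described are reused in the Alberta cohort, followed by: "Where appropriate, the RPM model will be re-calibrated by adjusting the baseline hazard and the mean values of the predictors". No trigger or threshold is given.

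**The concern.** The two sides of the comparison rest on different assumptions about censoring. The Weibull likelihood gives valid individual risks if censoring is independent of diabetes within levels of the predictors. A single Kaplan-Meier curve estimates the cohort's mean risk only if censoring is independent of diabetes without conditioning on anything. If women who conceive again tend to have lower diabetes risk, for example because they are younger, those who remain under observation are increasingly the higher-risk women. The Kaplan-Meier risk then exceeds the average of correct individual risks. This holds even if diabetes risk without a further pregnancy is accepted as the target.

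At stake is the overall calibration figure in both provinces. A shift in it is the usual reason to move a baseline hazard. Differences in birth spacing between Ontario and Alberta could therefore create or hide an apparent difference in calibration that has nothing to do with the model.

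**Working it through.** The article gives no figure for this measure, so there is none to reproduce. The check asks what observed/predicted would be for a model that is exactly right.

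**Anchors from the article (Sample size).** There were 2294 events in 756,956 person-years among 231,618 women.
- Rate: 2294/756,956 = 3.03 per 1000 person-years.
- Mean follow-up: 756,956/231,618 = 3.27 years.
- 5-year risk at constant hazard: 1 − exp(−5 × 0.00303) = 1.50%.

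**Source of censoring.** The last deliveries (31 March 2014) start follow-up about 30 September 2014 and have 4.5 years to 31 March 2019. Study end therefore cuts short only the latest deliveries, and most censoring before 5 years should come from conception.

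**Step 1: two groups, both exactly calibrated (group sizes, rates and conception shares assumed).**
- Younger: share 0.6, hazard 2.0 per 1000 per year, 75% conceive in 5 years, so c = −ln(0.25)/5 = 0.277 per year.
- Older: share 0.4, hazard 4.5 per 1000 per year, 25% conceive, so c = −ln(0.75)/5 = 0.0575 per year.

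Mean true risk = Σ w(1 − exp(−5h)) = 0.6 × 0.995% + 0.4 × 2.225% = 1.487%.

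The Kaplan-Meier estimate converges to 1 − exp(−∫h*(t)dt) over 5 years, where h*(t) = Σ w h exp(−(h+c)t) / Σ w exp(−(h+c)t). The pooled hazard h* starts at 0.6 × 2.0 + 0.4 × 4.5 = 3.00 per 1000. By year 5 the older group is 66% of the risk set and h* is 3.66 per 1000. The integral is 0.01667, so the Kaplan-Meier risk is 1.653%. The ratio is 1.653/1.487 = 1.11, a gap of 0.17 percentage points.

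Two variations:
- Milder contrast (2.5 v 3.8 per 1000; 70% v 35% conceiving): 1.559% v 1.498%, ratio 1.04, gap 0.06 points.
- Equal conception (55% in both groups, hazards as in the first case): ratio 1.00. The gap comes only from predictor-dependent censoring.

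**Step 2: age by GDM strata, with the event rate set to 3.03 per 1000 person-years.** The seven-fold GDM effect is from the Background section. Assumed inputs:
- GDM prevalence 6% at age 30.
- 5-year conception falling from 55% at age 20 to 3% at age 45 (moderate) or from 70% to 1% (strong), which gives 43 to 49% conceiving overall.
- Age hazard ratio 1.0 to 1.6 per 5 years.

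Kaplan-Meier/predicted, with the gap in percentage points:

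| Age HR per 5 years | Moderate | Moderate, conception concentrated early | Strong | Strong, conception concentrated early |
|---|---|---|---|---|
| 1.2 | 1.03 (0.04) | 1.04 (0.05) | 1.05 (0.07) | 1.07 (0.09) |
| 1.4 | 1.05 (0.07) | 1.06 (0.09) | 1.08 (0.11) | 1.11 (0.15) |
| 1.6 | 1.06 (0.09) | 1.08 (0.12) | 1.11 (0.15) | 1.14 (0.19) |

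Predicted risk in these cells is about 1.3 to 1.5%. At an age hazard ratio of 1.0 the ratio is about 1.01 to 1.02. With conception unrelated to predictors it is 1.00. If women with GDM conceive more often, the moderate case at hazard ratio 1.2 falls from 1.03 to 1.01, and the ratio among women under 35 drops to 0.98. The sign is therefore not guaranteed.

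**Step 3: simulation with a fitted Weibull model** (231,618 women, 12 replicates per scenario, age hazard ratio 1.4). Kaplan-Meier/fitted risk was 1.00 with no dependence, 1.04 with moderate and 1.08 with strong dependence. The relative standard error of the Kaplan-Meier risk was about 1.9%, so the bias is roughly 2 to 4 standard errors (0.04/0.019 = 2.1; 0.08/0.019 = 4.2).

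**Step 4: does standardising remove it?** In the same simulations, an age-stratified Kaplan-Meier averaged over the cohort gave observed/true risk of 0.99 (moderate) and 1.00 (strong), against 1.04 and 1.08 unstratified.

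**The case against.** A reader might infer that a perfectly calibrated model fails this check and will be recalibrated wrongly. The article does not support that. It sets no pass mark and rejects goodness-of-fit testing. Recalibration is foreseen only in Alberta, only where appropriate, and is not tied to this measure.

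The planned calibration by age group also answers much of the point. In the two-group example it would show 1.00 in each group beside an overall 1.11. With two age bands (under 35, and 35 or over) the age-only scenarios above give about 1.00 to 1.03. This stands, but it does not correct the overall value, and parity is not among the named groups.

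The inputs are weakly anchored, and this also stands. The article nowhere says how conception varies with age or parity. The two-group cases imply crude rates of 3.29 and 3.13 per 1000 person-years, somewhat above 3.03. A sharper contrast (2 v 6 per 1000) gives 1.15 but implies 4.06 per 1000, so it is left out of the range. The mean follow-up of 3.27 years does not demonstrate heavy censoring at conception either. If the 2014–2016 deliveries are calendar years followed from 6 months post-partum to March 2019, study end alone would give about 3.25 years. The follow-up rules behind those figures are not stated, so this is not decisive.

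Finally, an article may leave stratification or weighting to a fuller plan. But it does name the estimator, and unweighted is the natural reading.

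**Conclusion.** The point holds as a bias in the overall measure. If censoring at conception depends on the predictors, the unweighted Kaplan-Meier risk is not a valid benchmark for the mean predicted 5-year risk, even when the model is correct. Under the assumed patterns, observed/predicted is about 1.01 to 1.14. In absolute terms this is small, but it can exceed sampling error in a cohort of this size and be taken for real miscalibration.

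The size rests on assumed conception patterns and age effects, and the direction on how conception relates to all predictors jointly. For Alberta it further assumes the same censoring rule, which the External validation section does not restate. Wrong recalibration is a possibility, not a demonstrated consequence.

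**What to change.** Estimate the observed 5-year risk in one of two ways:
- with a Kaplan-Meier estimator weighted by the inverse probability of remaining uncensored, with censoring modelled on age, parity, GDM and the other predictors; or
- with Kaplan-Meier risks within predictor strata, averaged over the cohort distribution.

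Use the same estimator in Ontario and Alberta, and before any decision to adjust the baseline hazard. Report the unweighted value beside it, so that the effect of censoring is visible.

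Observed events divided by the summed predicted cumulative hazard to each woman's exit time, capped at 5 years, can be added as a supplementary check. Under a correct model, with censoring dependent on its predictors, this ratio is expected to be 1. It should not replace the main measure, because it gives more weight to early follow-up and does not directly assess 5-year risk.

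The cost is a sentence or two in the analysis plan and a little code. The downside is that a censoring model or set of strata must be specified, and the estimate becomes slightly more variable.

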### RPM predictive accuracy

Overall predictive accuracy will be assessed with the Brier score and by estimating explained variation using Nagelkerke’s *R*.

### RPM internal validation

To assess the degree of optimism in the estimated performance, internal validation using a bootstrapping approach, with 500 resamples will be performed. Using this approach, the model will be derived in each of the 500 bootstrap samples. Each of the bootstrap sample models will then be applied within the original dataset and measures of performance will be calculated for each bootstrap sample model. The difference in model performance between bootstrap sample models and the original model will be used to estimate the optimism corrected measures of performance, including Nagelkerke’s *R*^2^ and C-statistics. Over-fitting will be quantified by the calculation of a uniform shrinkage factor. Where necessary, the uniform shrinkage factor will be used to adjust the mode coefficients.

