**Methods:**

Data will be obtained from existing Ontario population-based administrative datasets. The derivation cohort will consist of all women who gave birth in Ontario, Canada between April 2006 and March 2014. Pre-specified predictors will include socio-demographic factors (age at delivery, ethnicity), maternal clinical factors (e.g., body mass index), pregnancy-related events (gestational DM, hypertensive disorders of pregnancy), and newborn factors (birthweight percentile). Incident type 2 DM will be identified by linkage to the Ontario Diabetes Database. Weibull accelerated failure time models will be developed to predict 5-year risk of type 2 DM. Measures of predictive accuracy (Nagelkerke’s *R*^2^), discrimination (C-statistics), and calibration plots will be generated. Internal validation will be conducted using a bootstrapping approach in 500 samples with replacement, and an optimism-corrected C-statistic will be calculated. External validation of the RPM will be conducted by applying the model in a large population-based pregnancy cohort in Alberta, and estimating the above measures of model performance. The model will be re-calibrated by adjusting baseline hazards and coefficients where appropriate.

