### Sample size

For the period between 2014 and 2016, there were 231,618 women who delivered a baby and 756,956 person-years of follow-up. Overall, 2294 women developed incident type 2 DM during follow-up (unpublished data). Using the criteria specified by Riley et al. and the *pmsampsize* R package, we calculated the minimum sample size required to be 6193 women to minimize overfitting and ensure the estimation of precise model coefficients [35, 36].

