### Analysis plan

All data manipulations will be carried out using Wickham’s *tidyverse* package [37] and modelling will be conducted using Harrell’s *rms* package in R [38]. The TRIPOD statement was used to devise the analysis plan and will be used to guide the reporting of the development and validation of the proposed model [39].

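### The bootstrap optimism rule, as worded, compares the wrong two quantities and removes only about half of the optimism; at the documented cohort size the effect is small

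*Protocol article*

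**What the plan says.** The section RPM internal validation in the protocol article gives the procedure in order.

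1. Refit: "the model will be derived in each of the 500 bootstrap samples".
2. Score: "Each of the bootstrap sample models will then be applied within the original dataset and measures of performance will be calculated" for each bootstrap model.
3. Correct: "The difference in model performance between bootstrap sample models and the original model will be used to estimate the optimism corrected measures of performance", with Nagelkerke's R-squared and the C-statistic named as the measures to be corrected.

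The Abstract (Methods) promises the same output: "an optimism-corrected C-statistic will be calculated". The Analysis plan section names the rms package for modelling, but neither section names a validation routine that would define the correction.

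**The concern.** The only performance described for the bootstrap models is their performance in the original data, and the only comparator named is the original model. The performance of each bootstrap model in the sample it was fitted to is the first term of the optimism estimate, and it does not appear. The article therefore does more than leave out a detail: it names the pair to be compared, and the pair is not the one that measures optimism.

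At stake is a reported result. The corrected C-statistic is the internal-validation figure announced in the abstract, and the validation results are to be published in full. A figure labelled as corrected that keeps about half of its optimism is wrong in the favourable direction.

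**Working it through.** The plan states no optimism figure, so there is none to reproduce. The rule itself can be checked.

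**Notation.** D is the original data and M the model fitted to it. D_b is a bootstrap sample and M_b the model derived in it. A(model, data) is performance.

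- Standard: O_std = mean over b of [A(M_b, D_b) − A(M_b, D)]
- As worded: O_word = A(M, D) − mean over b of [A(M_b, D)]

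The corrected value is A(M, D) minus the optimism. Under the wording this reduces to mean A(M_b, D), the average score of the refits in the original data. Each refit was trained on part of those same data: a bootstrap sample contains about 1 − (1 − 1/n)^n ≈ 1 − e^(−1) = 0.63 of the original subjects. That average is therefore itself optimistic.

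**Why about half.** On the log-likelihood scale with p parameters, M_b loses about p/2 relative to M when scored in D. It also gains about p/2 over M when scored in D_b. The standard rule adds both parts (p/2 + p/2 = p); the wording keeps only the first (p/2).

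**Inputs for the simulation.**
- Size: under Sample size, "there were 231,618 women who delivered a baby and 756,956 person-years of follow-up", with 2,294 events; 2,294 / 231,618 = 0.99%.
- Parameters: Table 1 sums to 32 to 36 df, depending on the BMI and glucose-challenge terms and taking the blank df for cardiovascular disease as 1. The value used was 36, with 130 as an assumed case with interactions.
- Assumed: a logistic model as proxy for the Weibull 5-year risk, normally distributed predictors, true C about 0.70 to 0.75.
- The model is refitted in every resample. True optimism is apparent performance minus performance in the target population.

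**C-statistic optimism**

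| n | events | parameters | datasets × resamples | true | standard | as worded | worded / standard |
|---|---|---|---|---|---|---|---|
| 6,193 | 61 | 36 | 60 × 40 | 0.1059 | 0.0838 | 0.0487 | 0.58 |
| 6,193 | 200 | 36 | 60 × 40 | 0.0433 | 0.0365 | 0.0190 | 0.52 |
| 20,000 | 400 | 36 | 20 × 25 | 0.0192 | 0.0193 | 0.0096 | 0.50 |
| 231,618 | 2,294 | 36 | 24 × 10 | 0.0045 | 0.0034 | 0.0018 | 0.51 |
| 231,618 | 2,294 | 130 | 3 × 6 | 0.0146 | 0.0127 | 0.0063 | 0.50 |

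**Nagelkerke R-squared optimism**

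| n | events | parameters | true | standard | as worded | worded / standard |
|---|---|---|---|---|---|---|
| 6,193 | 200 | 36 | 0.0489 | 0.0470 | 0.0243 | 0.52 |
| 20,000 | 400 | 36 | 0.0201 | 0.0201 | 0.0102 | 0.51 |
| 231,618 | 2,294 | 36 | 0.0035 | 0.0029 | 0.0015 | 0.50 |
| 231,618 | 2,294 | 130 | 0.0117 | 0.0109 | 0.0054 | 0.49 |

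Ratios were taken before rounding.

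**Residual error at the documented size, against the standard rule.**
- 36 parameters: C 0.0034 − 0.0018 = 0.0016; R-squared 0.0029 − 0.0015 = 0.0014.
- 130 parameters: C 0.0127 − 0.0063 = 0.0064; R-squared 0.0109 − 0.0054 = 0.0055.

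Against the simulated truth, the shortfall with 36 parameters is 0.0045 − 0.0018 = 0.0027 in C and 0.0035 − 0.0015 = 0.0020 in R-squared. The standard rule also fell short of the truth there, by 0.0011 and 0.0006. A separate simulation at n = 20,000 with about 400 events gave the same pattern for C: 0.021 standard, 0.011 as worded, 0.024 true.

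**The case against.** **The sentence may be a loose paraphrase.** The section's stated aim is to assess optimism, it already contains two steps of the standard method, and it does not say that the original data are the only place where the refits are scored. A standard validation routine would compute the right contrast. This stands as a caution about intent: one cannot conclude that the analysts will compute the wrong quantity. It does not rescue the text, because the correct contrast is stated nowhere. The pipeline also includes interaction selection, step-down and 10 imputed datasets, so purpose-written bootstrap code that follows the written rule is plausible.

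**The cohort is large.** This stands. A reader might take the results at n = 6,193 as the expected bias. That number is the calculated minimum, not the cohort to be analysed, and 61 events for 36 parameters is extreme overfitting. The counts used above are themselves for 2014 to 2016, whereas derivation covers April 2006 to March 2014. If eight years yield more events, the error is smaller still.

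**The model itself is unaffected.** This also stands. The rule changes only the reported internal performance. A shrinkage factor based on the calibration slope is the same under either rule, because the apparent slope is 1 in both. Bootstrap correction plays no part in the Alberta validation.

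**Two further readings lack support.** A reader might infer serious bias in subgroup performance, but the only assessment planned within predefined groups is calibration; no subgroup optimism correction is described. A reader might also infer that selection steps are not repeated in the resamples, but the section says that the model is derived in each one.

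**Conclusion.** The rule is wrong as written, and its bias runs one way: it recovers about half of the standard bootstrap correction (0.50 to 0.58 for C, 0.49 to 0.52 for R-squared), so the corrected figures are too favourable. At the documented size the residual error is about 0.002 in C and 0.001 in R-squared with 36 parameters. It is perhaps 0.006 and just over 0.005 with about 130 fitted terms, a figure that rests on an assumed term count and only three simulated datasets. The sizes also depend on the logistic proxy and assumed predictor effects; the factor of about one half does not depend on them closely. This is a minor correction of wording. The documents do not support a claim that the model, its coefficients, its external validation or the study's conclusions are compromised.

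**What to change.** Replace the sentence on the difference in performance with a definition along these lines: in each of the 500 bootstrap samples, re-derive the model; compute its performance in that bootstrap sample and in the original dataset; take optimism as the first minus the second; subtract the mean of the 500 values from the original model's apparent performance. Apply this to both the C-statistic and Nagelkerke's R-squared.

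The cost is one sentence and no new data. If the literal rule would otherwise have been followed, the reported C-statistic and R-squared will be slightly less favourable.
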